# Examining Feasibility, Acceptability, and Preliminary Outcomes of a Culturally Adapted Evidence-Based Postpartum Depression Preventive Intervention for Women in Doha, Qatar: Protocol for a Randomized Controlled Trial

**DOI:** 10.2196/11623

**Published:** 2023-08-11

**Keywords:** postpartum depression, intervention, prevention, cultural adaptation, Arabic

## Abstract

**Background:**

Postpartum depression and anxiety are the 2 most common perinatal mental health disorders, with prevalence rates higher among women living in the Middle East than in most Western countries. The negative outcomes associated with postpartum depression and anxiety are profound and include less responsive parenting and compromised infant and young child development. Although interventions exist to prevent postpartum depression and anxiety, to date, there have been no studies that have attempted to prevent postpartum depression or anxiety among Arabic-speaking women in the Middle East, including Qatar.

**Objective:**

The purpose of this study is to conduct a randomized controlled trial (RCT) of an evidence-based postpartum depression preventive intervention—Mothers and Babies (MB)—culturally adapted for use with Arabic-speaking women in Doha, Qatar. MB is guided by a cognitive behavioral therapy framework that focuses on increasing pleasant activities, promoting healthy thought patterns, and increasing the type and frequency of personal contacts. MB is tailored to specific needs and issues related to pregnancy and the postpartum period.

**Methods:**

A multidisciplinary and multiethnic investigator team adapted MB to promote cultural and contextual fit for Arabic-speaking women. Intervention concepts were reviewed to ensure core content would be understood by Arabic-speaking women in Qatar. Subsequently, images, activities, and examples in the intervention manuals were adapted, as needed, to make the content more relevant to Arab culture. To deliver the adapted intervention, 30 Arabic-speaking individuals with mental health backgrounds were trained. The adapted intervention was subsequently pilot-tested with 10 pregnant women receiving prenatal care at Sidra Hospital in Doha. We are now conducting an RCT to examine the effectiveness of the adapted intervention. We plan to enroll 210 pregnant individuals who are Arabic-speaking, with 1:1 randomization to the MB intervention or usual prenatal care. Among the enrolled participants, a stratified subsample of 40 pregnant women with diabetes is being recruited. Data collection will take place at baseline and a 6-month follow-up. The primary outcomes are depressive and anxiety symptoms and perceived stress. Diabetes self-care is the exploratory outcome for the subsample of individuals with diabetes. Intervention implementation will be assessed via client and provider surveys during and after intervention delivery. Power and sample size were calculated using a 2-sided 5% effort rate and assumed analyses on the individual level, accounting for attrition of 20%.

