### Power and Sample Size Calculations

With 105 participants recruited per study arm and an estimated attrition of 20%, the study will be able to detect an effect size of 0.5 in any of the 3 primary outcomes using the independent 2-tailed *t* test with a power of 80% and a significance level of .017.

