### Pilot Study of Adapted MB

A byproduct of this project is deepening the capacity of mental health professionals in Qatar to address mental health with their perinatal clients. As such, 29 individuals fluent in Arabic were trained on the adapted MB manuals. The individuals included graduate students from the Doha Institute for Graduate Studies’ new master’s in psychology program, medical students from Weill Cornell Medicine in Qatar, PMH nurses from Hamad Medical Corporation and Primary Health Care Cooperation, and nurses from Sidra Medicine. The nomination of these trainees was performed based on their medical backgrounds, prior experience with CBT, and availability to deliver the intervention during the time frame of the research study. Training was led by the 2 multiple principal investigators ([name] and [name]). Training occurred over a full day and introduced trainees to the MB intervention’s core concepts and implementation considerations. Subsequently, each intervention session was reviewed with key considerations highlighted by the trainers. Emphasis was placed on highlighting places in the curriculum where adaptations were made to promote cultural and contextual fit. A second training was held for 14 of the individuals who completed the first training and indicated an interest in facilitating MB intervention sessions. This second training provided these 14 individuals with details on the study’s intervention and research procedures (eg, facilitator responsibilities, patient recruitment process). Training was delivered in both Arabic and English.

For the pilot study, 4 of these facilitators delivered the MB intervention to 10 pregnant individuals. The average number of sessions received was 7.0 (out of 12), and 4 individuals completed all 12 sessions. Baseline assessments were conducted to pilot procedures and measures to be used in the RCT. Client and facilitator feedback was used to modify study procedures and slightly adapt the intervention content.

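### Power and primary analyses treat all women as independent, although MB-arm women share facilitators; any positive facilitator correlation makes the planned standard error somewhat too small

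*Protocol article*

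**What the plan says.** - **Power.** The Abstract (Methods) states that the calculation "assumed analyses on the individual level, accounting for attrition of 20" per cent, and "Power and sample size were calculated using a 2-sided 5% effort rate". Power and Sample Size Calculations gives the detail: "With 105 participants recruited per study arm and an estimated attrition of 20" per cent, the trial can "detect an effect size of 0.5 in any of the 3 primary outcomes" by an independent two-tailed t test "with a power of 80% and a significance level of .017".
- **Analysis.** Statistical Analysis compares the three primary outcomes by t test (Wilcoxon if highly skewed), then by linear regression adjusted for the baseline outcome and for observed imbalances between arms. Facilitator is not among the terms.
- **Delivery.** Allocation is "with 1:1 randomization to the MB intervention or usual prenatal care". Under Intervention Arm, MB is 12 sessions given by a trained mental health professional. Under Control Arm, women receive standard prenatal care and have no MB facilitator.
- **Number of facilitators.** The Abstract reports 30 people trained, and Pilot Study of Adapted MB reports 29. Of these, 14 who wished to facilitate had a further session: "This second training provided these 14 individuals with details" of the study's intervention and research procedures. In the pilot, "4 of these facilitators delivered the MB intervention to 10 pregnant individuals". The number delivering MB in the randomised trial is not given.

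**The concern.** A facilitator who sees several women over as many as 12 sessions can leave a common mark on their outcomes. If so, the MB-arm mean varies more than independent women would make it vary, while the control mean is unaffected. A t test or ordinary regression that ignores this understates the standard error of the arm difference and gives P values that are too small. An analysis that allows for it pays in power, and the sample size has almost no reserve to absorb the cost.

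This is not a complaint about detail left to an unseen analysis plan. The article itself states the individual-level assumption and names the tests, and its own description of delivery puts that assumption in doubt in one arm.

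**Working it through.** **Inputs from the article.** 105 women per arm and 20% attrition, so 105 × 0.8 = 84 analysed per arm; standardised effect 0.5 (SD 1); two-sided α = .017, so z = 2.387.

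**Inputs assumed.** Facilitators K = 14 (those given the study-specific training), with K = 30 for comparison; ICC 0.02 to 0.05; equal numbers of women per facilitator; equal total variance in the two arms.

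**1. The plan's own figure.** Under independence, SE = √(2/84) = 0.1543 and 0.5/0.1543 = 3.240. Power = Φ(3.240 − 2.387) = 80.3%. The exact t test gives 79.6%. The stated 80% reproduces, with nothing to spare.

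**2. Design effect in the MB arm only.** DE = 1 + (m − 1) × ICC, with m = 84/K. The true SE is √((DE + 1)/84), and its ratio to the planned SE is r = √((DE + 1)/2).

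- K = 14, m = 6, ICC 0.02: DE = 1.10, r = √1.05 = 1.025.
- K = 14, m = 6, ICC 0.05: DE = 1.25, r = √1.125 = 1.061.

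The planned SE is too small by 1 − 1/r, which is 2.4% and 5.7%.

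**3. Type I error of the planned t test.** α = 2 × [1 − Φ(2.387/r)].

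- ICC 0.02: 2.387/1.025 = 2.329, α = .020.
- ICC 0.05: 2.387/1.061 = 2.250, α = .024.

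**4. Power of an unadjusted analysis that allows for clustering.** Φ(3.240/r − 2.387).

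- ICC 0.02: Φ(3.162 − 2.387) = 78.1%.
- ICC 0.05: Φ(3.055 − 2.387) = 74.8%.

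**5. Rejection rate of the planned t test at an effect of 0.5.** Φ((3.240 − 2.387)/r).

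- ICC 0.02: 79.8%.
- ICC 0.05: 79.0%.

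**6. Sensitivity to the assumptions.**

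| Facilitators | Women each | ICC | SE ratio | True α, planned test | Power, clustering allowed for |
|---|---|---|---|---|---|
| 14 | 6 | 0.01 | 1.012 | .018 | 79.2% |
| 14 | 6 | 0.02 | 1.025 | .020 | 78.1% |
| 14 | 6 | 0.05 | 1.061 | .024 | 74.8% |
| 30 | 2.8 | 0.01 | 1.004 | .018 | 79.9% |
| 30 | 2.8 | 0.02 | 1.009 | .018 | 79.5% |
| 30 | 2.8 | 0.05 | 1.022 | .020 | 78.3% |

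Steps 2 to 6 use the normal approximation. Small-sample degrees of freedom would lower the clustering-corrected power a little further.

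**The case against.** **The two inputs that decide the size are not in the article.** This stands. Direction is certain for any positive ICC, but size is conditional. With 14 or more facilitators and an ICC of 0.02 or less, the power loss is about two points or less. MB is manualised, which should limit differences between facilitators, and nothing suggests that sessions are given in groups.

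**A reader might infer that the 80% is wrong.** The documents do not support that. The figure reproduces, the individual-level assumption is disclosed, and the planned test keeps about 79 to 80% rejection at the design effect size. The inflated type I error belongs to the planned test and the lower power to a corrected one. No single analysis suffers both in full.

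**A reader might carry the pilot's four facilitators into the trial.** Four people for 84 analysed women would mean 21 women each and much larger effects. But the pilot's load was 10/4 = 2.5 women each, which at 84 women would imply about 34 facilitators. No section says that four will deliver the trial.

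**A reader might infer that one or two strong facilitators could produce the result.** Nothing in the article bears on that.

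**Baseline adjustment may make up the loss.** Partly or fully, yes. The planned regressions adjust for the baseline outcome, whereas the power is for an unadjusted t test. If the baseline to follow-up correlation is 0.3 (assumed) and adjustment scales the SE by √(1 − 0.3²) = 0.954, corrected power with 14 facilitators is Φ(3.162/0.954 − 2.387) = 82% at ICC 0.02 and Φ(3.055/0.954 − 2.387) = 79% at ICC 0.05. This offsets the power loss; it does not by itself correct the type I error of a model that omits the facilitator.

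**A supporting model could be left to the analysis plan.** Fair as to its details. The assumption itself, however, is stated in the article.

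**Conclusion.** The concern holds in a limited form. The plan fixes an independence assumption that its one-arm facilitator delivery puts in doubt, and for any positive facilitator ICC the planned t test and regression understate the standard error. Under the central assumptions the main cost is a true error rate per outcome above the planned .017. Power falls below 80% only for an analysis that corrects for clustering, and baseline adjustment may restore it. With 30 facilitators both effects are minor. This calls for a supporting analysis and a clearer statement of the assumption, not a new primary analysis or a larger trial.

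**What to change.** - For each of the three primary outcomes, add a supporting partially nested mixed model: a random facilitator effect in the MB arm only, arm-specific residual variances, small-sample degrees of freedom, and adjustment for the baseline outcome.
- Report how many facilitators delivered MB in the randomised trial, and the estimated ICC for each outcome.
- Add to Power and Sample Size Calculations that the 80% assumes no facilitator clustering.

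**Cost.** Plan wording and one extra model per outcome. The link between woman and facilitator should already exist, because Data Collection Procedures and Study Assessments describes a facilitator survey timed from the start of delivery with a client. With 157 of 210 women enrolled at 31 March 2023, the model could at that date still be specified before follow-up was complete. The downside is slightly wider intervals, and an imprecise ICC if few facilitators deliver MB, which is a reason to keep the model as supporting.

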**Results:**

The cultural adaptation and pilot study of the adapted MB intervention are completed. A total of 157 women have been enrolled in the RCT as of March 31, 2023.

**Conclusions:**

This study is highly innovative, as it is the first study to our knowledge to examine the effectiveness of an evidence-based postpartum depression preventive intervention in the Middle East. Limitations include a single follow-up time point and a small subsample of individuals with diabetes.

**Trial Registration:**

ClinicalTrials.gov NCT04442529; https://www.clinicaltrials.gov/study/NCT04442529

**International Registered Report Identifier (IRRID):**

DERR1-10.2196/11623

## Introduction

Perinatal mental health (PMH) disorders are common and have significant impacts on women, their infants, families, and communities [1,2]. Postpartum depression and postpartum anxiety are the 2 most common PMH disorders [3,4]. Systematic reviews have found a pooled prevalence of 15.5% across studies conducted in high-income countries [5], while systematic reviews of studies conducted in low- and middle-income countries found a higher pooled prevalence of 24.7% [6]. Among low- and middle-income countries, the highest prevalence rates were found in the Middle East and North Africa. Studies conducted in Qatar have found postpartum depression prevalence rates ranging from 18.6% to 27.3% [7,8].

An array of efficacious interventions exist that prevent postpartum depression [9,10], with several of these interventions demonstrating effectiveness in improving anxiety symptoms given the comorbidity with postpartum depression [11]. One intervention that has demonstrated efficacy in reducing depressive and anxiety symptoms and preventing the onset of new cases of postpartum depression is the Mothers and Babies (MB) course [12-15]. MB is a manualized intervention guided by a cognitive behavioral therapy (CBT) framework. CBT is characterized by a focus on (1) increasing pleasant activities, (2) focusing on one’s thoughts, and (3) the type and frequency of personal contacts (ie, social support). MB contains a module in each of these 3 areas. The content of MB is tailored to specific needs and issues related to pregnancy and the postpartum period.

Despite the prevalence rate of postpartum depression exceeding those found in Western countries and the availability of interventions effective in preventing postpartum depression, to date, there have been no intervention studies that have attempted to prevent postpartum depression among Arab women in the Middle East and North Africa region, including Qatar. The overarching goal of this study is to examine the feasibility, acceptability, and outcomes associated with MB delivered to women in Doha, Qatar. However, because MB was developed and previously examined when delivered to Western pregnant women, cultural adaptation was required before rigorous testing of the intervention in Qatar. The specific aims of this study are:

To adapt MB for use with Arab Arabic-speaking women in Qatar. Cultural and contextual adaptations were undertaken by a multidisciplinary and multiethnic research team.To conduct a small pilot study (n=10) that examines the acceptability, appropriateness, and feasibility of the adapted MB intervention when delivered to Arab Arabic-speaking women in Qatar. Pilot study findings are used to make final revisions to intervention and research protocols.To conduct a randomized controlled trial (RCT; n=210) to determine the effectiveness of the adapted MB intervention on depressive symptoms, anxiety symptoms, and perceived stress among Arab Arabic-speaking women in Qatar. Our primary hypothesis is that women receiving the adapted MB intervention will exhibit greater reductions in depressive symptoms, anxiety symptoms, and perceived stress compared to women not receiving the intervention.

A subaim is to recruit a stratified random sample of 40 women with diabetes (n=20 control group; n=20 MB intervention) and examine intervention effects on mental health outcomes as well as diabetes self-management.

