### Randomization Procedures and Intervention Conditions

#### Randomization Procedures

Stratified permuted block randomization with blocks of sizes 2 and 4 will be used to randomize consenting women into the control arm or the intervention arm in a one-to-one fashion. The stratification will be based on the diabetic status of the woman. The randomization will be done by a statistician who is not involved in recruiting patients. A randomized list was created by the biostatistician, which was later uploaded to Research Electronic Data Capture (REDCap; Vanderbilt University) [18,19], a web-based software package for data management. This allows for the lack of human involvement on the part of the research team in the assignment of a participant to a group. It also allows for the on-the-spot assignment of participants into either the control or intervention groups.

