#### Intervention Arm

Women randomized to the intervention arm will receive the culturally adapted MB intervention. MB consists of 12 sessions, each designed to last 15-20 minutes. The first 2 sessions provide (1) an understanding of the emotional and physical outcomes associated with stress, including concerns related to parent-child interaction, (2) strategies to notice one’s mood, and (3) an overview of how the remaining CBT content can help minimize stress levels. Sessions 3-5 focus on the CBT module of Pleasant Activities, while sessions 6-8 focus on Thoughts, and sessions 9-11 focus on Contact with Others. Session 12 is a course wrap-up and graduation. Intervention sessions provide concrete skills participants can use—for example, developing lists of pleasurable activities and strategizing how to overcome obstacles to engage in those activities. At the end of each session, a short personal project is provided to participants to encourage skill practice prior to the next session. Intervention sessions are delivered in-person, by phone, or via telehealth (Zoom and Microsoft Teams) by a mental health professional trained in MB. Sessions are intended to be delivered weekly or every other week, with flexibility given to deliver sessions at the same time to facilitate the timely completion of the intervention. Incentives will be provided to participants after completing each MB module to encourage their continued intervention participation. Additional content was added to selected sessions for the diabetic subgroup. This content was intended to draw links between the core MB cognitive-behavioral skills and diabetes management and self-care. For example, content that indicates how exercise and a healthy diet—aspects that are important for diabetes management—are also related to mental health, as both interventions have a positive effect on mental and emotional well-being, was added.

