### Statistical Analysis

A flowchart will be constructed based on the CONSORT (Consolidated Standards of Reporting Trials) guidance to show the number of recruited, excluded, lost to follow-up, and analyzed participants. Descriptive statistics will be used to summarize baseline characteristics overall and by study arm. As appropriate, mean (SD) and frequency (proportions) will be used to summarize continuous and categorical variables, respectively. Median (IQR) will be used in cases of skewed or nonnormal distributions. Analyses will use normal theory methodology as appropriate, and in cases of violations of assumptions, transformations or nonparametric analyses may be used. We will use SPSS (version 27; IBM Inc) to perform all analyses.

Analyses will be done using the intent-to-treat principle and will compare the 3 primary outcomes between study arms using the independent 2-tailed *t* test (or the Wilcoxon rank sum test in cases where outcomes were highly skewed). The analyses above will be repeated using univariate linear regression to be able to adjust later for any imbalances in baseline characteristics between the study arms and the baseline values of the primary outcomes. Additional analyses will include fitting multivariate linear regression models for each of the 3 main outcomes to assess the effectiveness of the intervention while adjusting for the baseline value of the outcome and any observed imbalances in participants between the 2 study arms. Unadjusted and adjusted mean differences in the primary outcomes between the 2 study arms will be presented along with their standard deviations and *P* values. For the primary outcomes, missing data at 6 months will be imputed using the average of the patients in that group or other methods such as multiple imputation by chained equations, and the primary analyses will be repeated as a sensitivity analysis. Secondary outcomes will be analyzed by comparing study arms using the chi-squared test (or Fisher exact test if expected cell counts are below 5) for categorical outcomes and the independent 2-tailed *t* test (or Wilcoxon rank sum test for highly skewed data) for numeric outcomes. Compliance with the intervention will be assessed by counting the number of intervention sessions received.

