Because each MB session lasts only about 20 minutes, sessions can be delivered during an existing health care visit (eg, while waiting for a prenatal care appointment). MB is also highly flexible, allowing for intervention delivery in person, by phone, or via telehealth (eg, Zoom, Microsoft Teams). The use of non-face-to-face interventions may be of particular benefit to women who struggle to attend prenatal appointments—for example, if women do not feel well, have a child who is unwell, or have difficulty accessing transportation or childcare. The use of phone or telehealth approaches allows for the intervention to be more easily delivered during very hot weather or during Ramadan—important contextual considerations for interventions delivered to women in Qatar and the Middle East.

This study is not without limitations. Although the adaptation of MB was conducted to promote cultural and contextual fit, caution will need to be used in generalizing findings beyond the sample recruited from one medical center in Doha. Our 6-month follow-up time point is also limited in its ability to examine sustained intervention effects as well as the impact of the intervention on parenting or parent-child attachment outcomes. Although the diabetic subsample is innovative, our sample size is limited for this exploratory aim.

Pregnancy and the early postpartum period are times of increased risk of mental health disorders—particularly depression and anxiety—that impact not only maternal and fetal well-being and functioning but also mother-infant attachment, parenting practices, and infant development. These time periods are opportune times for mental health interventions given that women access health care more frequently and families are often more motivated to engage in health-promoting activities to promote positive outcomes for their children. This study has the potential to add to the evidence base on postpartum depression preventive interventions broadly and will also be the first of its kind to do so among exclusively Arab women in the Middle East.

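### The diabetes subaim on mental health outcomes would be better served by adding diabetic stratum and arm-by-stratum to the planned full-sample regressions than by a comparison of 20 against 20

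*Protocol article*

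**What the plan says.** The specific aims in the Introduction include a subaim for women with diabetes ("n=20 control group; n=20 MB intervention"). Its purpose is to "examine intervention effects on mental health outcomes as well as diabetes self-management". No test, significance level or rule of interpretation is attached to it there.

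Three other parts of the Methods bear on it:

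- Randomization Procedures: "The stratification will be based on the diabetic status of the woman".
- Intervention Arm: "Additional content was added to selected sessions for the diabetic subgroup". The additions link the core skills to diabetes management.
- Statistical Analysis: the arms are compared by t test or Wilcoxon test and by regression. "Additional analyses will include fitting multivariate linear regression models for each of the 3 main outcomes", with adjustment for the baseline value of the outcome and for imbalances seen between the arms. Diabetic status is not named as a covariate or as a modifier of the effect.

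The Power and Sample Size Calculations section covers only the whole trial. The Abstract and the Data Collection section name diabetes self-care as the exploratory outcome. The Abstract lists the small diabetes subsample as a limitation, and the Discussion concedes that "our sample size is limited for this exploratory aim".

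**The concern.** The three mental health outcomes are measured in all 210 women, about 170 of whom will not have diabetes (210 − 40). Diabetes self-care is different, because it is an outcome for the diabetes subsample only. For the mental health outcomes, an analysis of the 40 women alone sets aside what the rest of the trial can say, and it is very small.

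A P value from within the subsample also mixes two things: how large the effect is in women with diabetes, and how few of them there are. It cannot say whether the effect differs between the strata. That comparison is of interest here because the trial randomises by diabetic status and gives women with diabetes in the intervention arm some extra content.

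The covariate rule in Statistical Analysis does not help. It brings in variables that turn out imbalanced, and stratified blocks keep diabetic status balanced between the arms. Applied literally, the rule would leave out the one factor on which randomisation was stratified.

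What is at stake is how the subaim is reported. A significant overall result beside a non-significant one in women with diabetes is a common pattern under equal effects, and it is easily misread unless the plan says how to read it.

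**Working it through.** **Inputs.** From Power and Sample Size Calculations: "With 105 participants recruited per study arm and an estimated attrition of 20" per cent, and "the study will be able to detect an effect size of 0.5 in any of the 3 primary outcomes", with 80% power and a significance level of .017. From the Introduction: 20 women with diabetes per arm. Assumed: the same attrition in both strata, outcome SD 1, and .05 or .017 (two-sided) for the subsample, since no level is stated for it.

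**1. The plan's own figure.** Analysed per arm: 105 × 0.8 = 84. For a two-sample t test the noncentrality is d/√(2/n) = 0.5/√(2/84) = 3.24. At .017 the noncentral t gives 79.6% power (normal approximation 80.3%). The stated 80% is reproduced.

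**2. Power in the subsample alone at d = 0.5.** Analysed per arm: 20 × 0.8 = 16. Noncentrality: 0.5/√(2/16) = 1.41, or 0.5/√(2/20) = 1.58 without attrition.

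| Women per arm | Power at .05 | Power at .017 |
|---|---|---|
| 20 (no attrition) | 34% | 19% |
| 16 (20% attrition) | 28% | 15% |

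With 16 per arm at .05, 80% power is reached only for an effect of about 1.02 SD. An effect of 0.5 SD would need 63 analysed per arm. Baseline adjustment with an assumed correlation of 0.5 raises the 28% to about 35%.

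**3. How often the two results would disagree.** In a simulation of 100,000 trials with the same true effect in both strata (16 and 68 analysed per arm), the pattern counted was overall p < .017 with diabetes-only p ≥ .05, for one outcome.

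| Common true effect (SD) | Share of trials with the pattern |
|---|---|
| 0.5 | 54% |
| 0.4 | 42% |
| 0.35 | 33% |
| 0.3 | 25% |

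At 0.5, the 54% amounts to 68% of the trials that are significant overall. At 0.35 and below, the commonest result is that neither test is significant (51% at 0.35).

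**4. What the full-sample model would give.** Women without diabetes analysed per arm: 84 − 16 = 68.

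- SE of the effect with diabetes: √(2/16) = 0.354 SD.
- SE of the effect without diabetes: √(2/68) = 0.171 SD.
- SE of the difference: √(2/16 + 2/68) = 0.393 SD.
- 95% CI half-width for the difference: 1.975 × 0.393 = 0.78 SD (164 df).
- Difference detectable with 80% power: 2.802 × 0.393 = 1.10 SD.
- 95% CI half-width for the effect with diabetes: 2.042 × 0.354 = 0.72 SD from the subsample alone (30 df), and 1.975 × 0.354 = 0.70 SD from the full model.
- If the effect were 0.5 SD without diabetes and zero with it, the interaction test at .05 would detect this about 24% of the time.

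**The case against.** The strongest reply is that no stand-alone analysis is specified. The subaim is one sentence in the Introduction, and a model with an arm-by-diabetes term would satisfy it word for word. Subgroup model terms are commonly left to an analysis plan, and that plan is not shown. This stands: the within-subsample comparison is the natural reading of a 20-against-20 subaim, but it is a reading. The absence of an interaction term from a condensed article is not in itself a fault.

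A reader might go further and infer that the trial is set to report a misleading lack of effect in women with diabetes. The article does not support that. It nowhere says that a non-significant result will be read as no effect, it calls the aim exploratory, and it discloses the small subsample twice. Nor is the discordant pattern the likeliest result under every plausible effect, as the table in step 3 shows. It is also counted per outcome: with three independent outcomes tested at .05, at least one would be significant in the subsample in up to 62% of trials with 16 per arm, or 71% with 20.

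It is also fair to say that the interaction test is no stronger. Its 24% power against a complete absence of effect in women with diabetes means that a null interaction could be misread as equal effects. So the protection comes from reporting estimates with intervals and from a stated reading rule. The interaction term does not restore power.

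What the reply leaves untouched is the covariate rule. It is stated for these same three outcomes, and it would pass over the stratification factor.

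**Conclusion.** The point holds as a low-cost improvement, not as an error in the plan. The article commits to examining mental health effects in 20 against 20 women. Read as a within-subsample comparison, that has about 28% power per outcome at .05 (15% at .017) for the planning effect, and it cannot address whether the effect differs by diabetic status. The regressions planned for the same outcomes do not name the stratification factor. These figures rest on 20% attrition in both strata, a true effect of 0.5 SD, and significance levels that the article does not give for the subsample. Without attrition, power is 34% and 19%.

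The stronger reading, that the design will produce a false conclusion of no effect in diabetes, should not be drawn. It needs a rule of interpretation that the article does not contain.

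**What to change.** In Statistical Analysis, and by cross-reference in the subaim:

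1. Add diabetic stratum to the full-sample regressions already planned for depressive symptoms, anxiety symptoms and perceived stress.
2. For the subaim, add arm-by-stratum to those models. Report the effect in women with diabetes, the effect in women without, and their difference, each with a 95% CI, labelled as exploratory estimates.
3. State that a non-significant effect in women with diabetes does not show no effect, and that a non-significant interaction does not show equal effects.
4. Keep the subsample-only comparison for diabetes self-care.

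The cost is a few sentences and two extra model terms, with no new data, staff or participants. The wording should be settled before any analysis by arm; the article reports recruitment as still in progress. The downside is limited precision: the difference will be imprecise, and the interval for women with diabetes barely narrows (half-width 0.72 to 0.70 SD). If the unseen analysis plan already contains these terms, a cross-reference is enough.
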